### Control group

Participants allocated to the control group will receive the same educational materials as those in the intervention group. The educational content is consistent across both groups; however, in the intervention group it is delivered interactively within supervised sessions, while in the control group it is provided in a self-directed format. These will cover topics including exercise, nutrition, mobility changes, fatigue, optimising bone health, pain management, mental health, sleep and physical activity maintenance. These materials will be delivered weekly via email over the 8 week study period. Participants in the control group will not be prescribed a structured exercise programme during the study period. Following completion of the 8-week programme, participants in the control group will receive access to the same exercise videos and will be offered the opportunity to take part in an optional online exercise class.

Participants in both groups will be asked to continue their usual activities and will not be instructed to modify or stop any existing physical activity. The intervention is described in accordance with the TIDieR (Template for Intervention Description and Replication) checklist to support replicability.
^29^

## Data collection

### Outcomes

Six domains of an evidence-based framework for feasibility studies will be evaluated: demand, implementation, practicality, potential efficacy testing, adaptability and acceptability
^21^ (
Table 1). Each domain will be assessed using predefined metrics as outlined in
Table 1, including recruitment rate (demand), attendance and exercise completion (implementation), adverse events (practicality), qualitative interviews exploring acceptability and adaptability, and changes in physical, mental and social outcomes (potential efficacy). These findings will inform progression to a larger, fully powered trial.

**Table 1. T1:** CP-Excel outcomes.

Domain	CP-Excel Outcomes
Demand	Recruitment rate
Implementation	Fidelity to the programme: Attendance at each class and completion of the exercise programme
Practicality	Recording of adverse events
Adaptability	Semi-structured interviews with adults with CP
Acceptability	Semi-structured interviews with adults with CP
Potential efficacy	Physical, mental and social outcomes

### Assessments

All participants will complete self-reported assessments at baseline (0 weeks) and immediately after participation in the eight week programme. Assessments may be completed online, on the phone, in person with the post-doctoral research fellow or on paper. Participants who complete paper versions will be given a freepost envelope to return the completed forms. The online outcome measures will be hosted on REDCap, an online survey platform.

The following data will be collected at baseline only:

1. Socio-demographic
a.Ageb.Gender

2. Condition-specific information
a.Type of CPb.GMFCS levelc.Intellectual disabilityd.Secondary impairments

The data shown in
Table 3 will be collected at baseline and follow-up:

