**Figure 1. f1:**
[figure not shown]
CP-Excel study design.

All participants will complete a brief screening survey which includes personal details (name, email/phone number), and any health concerns that may prevent them from safely engaging in the exercise programme. Medical stability will be assessed through self-report in this survey, including information on current health conditions and any contraindications to exercise, and clarified through follow-up discussion with the research team where required. The ability to participate in the study will also be assessed during screening and initial interaction with the researcher, considering communication, cognitive ability, and ability to follow instructions. Where appropriate, the potential for support from a family member or caregiver and the feasibility of making adaptations will be considered to facilitate participation. After the screening process, participants who meet the eligibility criteria will be asked to provide informed written or electronic consent to the post-doctoral research fellow.

Following screening and consent, all participants will undergo a baseline assessment via an online survey. Participants will be randomised to the intervention or control group, and then re-assessed at the end of week 8.

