### Randomisation

Following the baseline assessment, participants will be randomly allocated to either an intervention or control group in a 1:1 ratio. Stratification will be based on their mobility status: GMFCS Level I-III (with or without walking aids) and GMFCS Levels IV-V (who use wheelchairs). The random allocation will be generated by a computer in random permuted blocks of 2 or 4, and implemented automatically within REDCap (Research Electronic Data Capture). Allocation concealment will be ensured as the sequence is embedded within REDCap and not accessible to the research team prior to assignment.

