The programme will be delivered by a physiotherapist (post-doctoral research fellow) and a specialist personal trainer in exercise for long-term neurological conditions. The programme content was developed with input from physiotherapists and personal trainers with expertise in CP, and from the Public and Patient Involvement (PPI) contributors who are adults with CP. The exercise programme will be piloted with PPI contributors in advance of the intervention commencing: any necessary refinements will be made based on feedback received. This will include refinement of adaptations to support delivery across a range of abilities and needs. During the intervention, adaptations will be informed by participant feedback and session experience. All adaptations made during programme delivery (e.g., modifications to exercises, level of support, or delivery approach) will be documented prospectively by the researcher delivering the intervention. The researcher delivering the programme will review sessions, document adaptations and implement any necessary adaptations in subsequent group classes. These documented adaptations will inform ongoing refinement of the intervention, interpretation of feasibility outcomes, and future implementation.

Detailed intervention materials, including exercise and educational content, will be made available alongside the publication of the study findings, informed by the feasibility outcomes.

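### Outcome forms may be completed in person with the fellow who teaches the intervention classes, and two sections disagree on baseline mode, so a change of mode at week 8 can add arm-related reporting bias to the exploratory PROMIS changes

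*Protocol article*

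**What the plan says.** Four parts of the protocol article bear on this.

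- **Assessments.** Both time points rest on self-report: "All participants will complete self-reported assessments at baseline (0 weeks) and immediately after participation in the eight week programme". On how the forms are filled in: "Assessments may be completed online, on the phone, in person with the post-doctoral research fellow or on paper". The online version is hosted on REDCap, and paper forms come back by freepost.
- **Recruitment (text after Figure 1).** Baseline is described differently: "Following screening and consent, all participants will undergo a baseline assessment via an online survey".
- **Intervention group.** On who runs the classes: "The programme will be delivered by a physiotherapist (post-doctoral research fellow) and a specialist personal trainer in exercise for long-term neurological conditions".
- **Randomisation and Control group.** Allocation comes after baseline: "Following the baseline assessment, participants will be randomly allocated to either an intervention or control group in a 1:1 ratio". Controls have no classes during the study period. Of their educational materials the article says: "These materials will be delivered weekly via email over the 8 week study period".

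The Quantitative data analysis section plans linear mixed models comparing the groups over time for the PROMIS outcomes, on available cases and without multiple imputation. It calls the outcome analysis exploratory. The Discussion adds that the outcome data will feed the design and sample size of a later, larger trial.

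**The concern.** The person named for in-person completion is also an instructor of the intervention arm. By week 8 that person has taught one arm for eight weeks and knows who was in it. Answers on mood, self-efficacy, pain and fatigue given face to face to one's own instructor may be more favourable than answers given alone on a screen.

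If the Recruitment section governs baseline and the Assessments section governs week 8, anyone not followed up online changes mode between visits. A change of mode within a person is mixed up with time. If its frequency or its effect differs by arm, it is also mixed up with treatment, and a group-by-time model cannot separate the two.

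The stake is limited, because this trial does not test effectiveness. Still, a distorted between-arm change could be carried into the planning of the next trial. Outcome assessment is also one of the procedures whose feasibility the Study design section sets out to examine, so knowing which modes were used, and with whose help, is useful in itself.

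**Working it through.** **Step 1. Compare the two statements on mode.** Recruitment gives one baseline mode, online, for all. Assessments gives four modes and covers both baseline and the end of the programme. Both cannot hold for baseline.

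**Step 2. Follow each reading.**
- If Assessments governs both visits, a participant who needs help can have the same help twice. No switch is forced, but none is prevented.
- If Recruitment governs baseline and Assessments governs week 8, all baselines are online. Every participant assessed by phone, on paper or in person at week 8 has then switched.

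**Step 3. Locate where an arm difference can enter.** Randomisation follows baseline, so baseline mode cannot depend on allocation. Week-8 mode can, and so can the response to the fellow at week 8.

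**Step 4. Scale, for illustration only.** The plan states no figure to reproduce. Let p be the share of an arm that self-completes at baseline and answers to the fellow at week 8, and let m be the mean shift this causes in T-score points. The bias in the between-arm difference in change is

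B = pI × mI − pC × mC

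where I is intervention and C is control. The documents give none of these four inputs. The values below are assumptions.

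| Assumed case | Calculation | B (points) |
|---|---|---|
| Equal shares, equal shift | 0.30 × 2 − 0.30 × 2 | 0 |
| Shares 30% and 10%, shift 1 | (0.30 − 0.10) × 1 | 0.2 |
| Shares 30% and 10%, shift 2 | (0.30 − 0.10) × 2 | 0.4 |
| Shares 30% and 10%, shift 3 | (0.30 − 0.10) × 3 | 0.6 |
| Shares 50% and 0%, shift 5 | (0.50 − 0) × 5 | 2.5 |
| Equal shares of 30%, shift of 2 in the intervention arm only | 0.30 × 2 − 0.30 × 0 | 0.6 |

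The last row shows that unequal switching is not required. It is enough that the fellow's presence affects only those whom the fellow has taught.

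**Step 5. Compare with sampling error.** The plan allocates 30 per arm. With an assumed SD of 10 and full follow-up, the standard error of the between-arm difference is 10 × √(2/30) = 2.58 points. Adjusting for baseline multiplies this by √(1 − r²). At r = 0.5 it is 2.58 × 0.866 = 2.24, and at r = 0.8 it is 2.58 × 0.6 = 1.55. A bias of 0.4 is therefore about 0.15 to 0.26 standard errors, and a bias of 2.5 is about 1.0 to 1.6. The assumptions decide the answer.

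**The case against.** The strongest reply is that nothing in the article says anyone will switch mode, or that switching will differ by arm. The four modes are offered equally to both arms at both visits. Need for help plausibly follows impairment, which is present before randomisation, and allocation is stratified by GMFCS group. The online-survey sentence sits in a procedural overview and may be only a loose summary. The fellow is named for in-person completion only. Who conducts phone assessments is not stated, and online and paper forms need no fellow. Open allocation with self-report permits courtesy bias in any mode. Flexible modes are a sound accessibility measure in this population. A condensed article may also leave rules on mode consistency to the full protocol or to the data management plan, which is under review.

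Most of this stands, and it limits the point to a possible bias. It does not remove it. The permission for a class instructor to be present at outcome completion is stated in the article, and so is the disagreement over baseline mode. Neither is an omission.

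A reader might infer something stronger: that the arrangement does bias the PROMIS results towards the intervention, by a definite amount such as 0.4 points and in one direction across all 11 PROMIS forms in Table 3. The documents do not support that. They give no mode shares and no mode effect, equal shares with equal shifts give zero, and the Efficacy section notes that scoring direction varies by domain.

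**Conclusion.** The point holds as a risk. The article lets a participant complete baseline online and then complete week 8 with the fellow, who is by then the instructor of one arm only. That can add arm-related reporting bias to the PROMIS changes. Whether it does, and by how much, cannot be worked out from the documents. The illustrative range of 0 to 2.5 T-score points rests wholly on assumed shares (0% to 50%), assumed shifts (1 to 5 points) and, for comparison with sampling error, an assumed SD of 10.

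The consequence is moderated by the exploratory status of the outcome analysis. It is still worth settling, because the data are meant to inform the next trial, the remedy is cheap, and a mode or helper that was not recorded at the time may be impossible to recover.

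**What to change.** 1. Reconcile the Recruitment and Assessments sections so that they give the same account of how baseline may be completed.
2. Make self-completion the default at both visits, by REDCap or freepost paper, with the participant's own supporter if needed.
3. Use each participant's baseline mode again at week 8 where possible. If it is not possible, take the assessment in another mode. A missing form is the worse outcome, because the analysis uses available cases only.
4. Where an existing team member who does not run classes is available, prefer that person over the fellow for assisted week-8 completion. The article does not show that such a person exists, so this should be a preference and not a requirement.
5. Record mode and helper at each visit and report both by arm. Keep any analysis by mode descriptive. Excluding participants because of their week-8 mode or helper would condition on an event after randomisation, and would probably remove the more impaired participants from a trial of 60.

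The cost is one extra data field, a short protocol edit and slightly less flexibility at week 8.

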### Demand

Demand will be assessed by recording recruitment rate to the programme. This will include recording the total number of people who responded to invitations or advertisements to participate in the study, the number of potentially eligible participants identified over a 3-month period, the proportion of eligible participants who provided consent to participate, and the reasons for exclusions or decisions to decline participation.

### Implementation

Implementation will be assessed by recording:
•Attendance at sessions to evaluate fidelity to intervention receipt.•Self-reported completion of the prescribed exercise programme to evaluate fidelity of intervention content. Participants in the intervention group will complete a brief weekly survey indicating whether they completed the prescribed exercises independently at least twice per week in addition to the supervised session.

Practicality will be assessed by recording adverse events reported by participants in both groups at each assessment time point.

**An Adverse Event (AE)** is defined as any untoward medical occurrence affecting a participant that does not necessarily have a causal relationship with the intervention (
https://www.ct-toolkit.ac.uk/glossary).

**A serious adverse event (SAE)** is defined untoward medical occurrence/effect that:
(a)results in death;(b)is life-threatening;(c)requires hospitalisation or prolongation of existing hospitalisation;(d)results in persistent or significant disability or incapacity.

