## Intervention group: Online exercise and education programme

The intervention is an 8-week online exercise and education programme consisting of an online exercise class once per week, in accordance with exercise prescription guidelines for people with CP.
^7^ The programme will consist of eight weekly group sessions, each lasting 60 minutes. Each session will include (i) 5–8 minutes for warm-up, a 30 minute exercise programme, 5 minutes for cool-down, and (ii) 15–20 minutes of interactive learning focused on a topic of relevance to adults with CP.

The online exercise class will focus on mobility, strength and balance exercises for major muscle groups, based on the most common reasons that adults with CP seek physiotherapy.
^15^ Balance will be both explicitly targeted and integrated within functional exercises throughout the programme. Participants will complete up to 10–11 exercises in each class. In standing, balance will be challenged through functional tasks such as sit-to-stand, squats, side stepping, toe taps and exercises involving weight shifting or changes in base of support. The exercises may be completed in sitting or standing depending on the person’s ability. For participants exercising in sitting, balance will be addressed through trunk control and postural stability activities, such as unsupported sitting, reaching tasks, and dynamic upper limb movements performed within a safe and supported environment. The intervention will be tailored to individual ability, with exercises adapted based on mobility level (GMFCS I-V), upper limb function, associated impairments (e.g. communication, vision, or hearing) and risk assessment findings, while maintaining a consistent overall structure. Where required, participants may be supported by a family member or caregiver to assist with communication, technology use, or safe participation. Participants will complete between 2 and 4 sets of 6–15 repetitions of each exercise. Exercises will focus on functional, task-oriented movements targeting mobility, strength, and balance. The programme will emphasise controlled, submaximal effort and movement quality rather than maximal or high-velocity (power-based) training. Exercise intensity will be individualised and guided by participant ability, with participants encouraged to work at a moderate level that is challenging but safe.

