Participants will also be encouraged to repeat the exercises independently twice per week between sessions. Participants will be provided with access to private exercise videos demonstrating the exercises performed during the online sessions to support independent completion. Adherence to the intervention will be recorded through attendance at online sessions and a brief self-reported survey capturing whether participants completed the prescribed exercises independently at least twice per week. The number of sets and repetitions performed during supervised sessions will also be recorded, with progression guided by participant ability over the 8-week programme. Progression will be achieved by modifying repetitions, sets, range of movement, level of support, and exercise complexity, rather than through one-repetition maximum testing. Examples of exercises include overhead reach, Table or box push-ups, Lateral arm raises, Knee up, hip back or wheelchair dip, side step or hip out, sit to stand, squat, knee straight/bend, heel raises and seated rowing as well as balance-focused activities such as weight-shifting and reaching tasks. For example, exercises such as squats may be performed in standing with or without support or adapted to seated alternatives (e.g., sit-to-stand or wheelchair-based upper body movements) to accommodate different mobility levels. Exercises will be demonstrated with options and progressions to enable participation within a group setting while accommodating individual differences. Verbal cueing and demonstration will be used to guide correct technique, pacing, and safe execution of movements during each session.

The 15–20 minute interactive learning component of each weekly online class will consist of educational materials on exercise, nutrition, mobility changes, fatigue, optimising bone health, pain management, mental health, sleep and physical activity maintenance (one topic per week). Educational materials and exercises will be delivered during the online class. The educational content is consistent across both study groups; however, in the intervention group it is delivered interactively during weekly sessions.

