### Acceptability

*Acceptability* will be assessed by conducting semi-structured interviews with 15 adults with CP who participated in the online exercise programme using the theoretical framework of acceptability
^30^ to inform topic guides and data analysis. The seven component constructs that represent acceptability are detailed in
Table 2 and include: affective attitude, burden, perceived effectiveness, ethicality, intervention coherence, opportunity costs, and self-efficacy.
^31^

**Table 2. T2:** Theoretical framework of acceptability components.
^31^

Components	Description
Affective Attitude	How an individual feels about the intervention
Burden	The perceived amount of effort that is required to participate in the intervention
Ethicality	The extent to which the intervention has good fit with an individual’s value system.
Intervention Coherence	The extent to which the participant understands the intervention and how it works
Opportunity Costs	The extent to which benefits, profits or values must be given up to engage in the intervention.
Perceived Effectiveness	The extent to which the intervention is perceived as likely to achieve its purpose.
Self-Efficacy	The participant’s confidence that they can perform the behavior required to participate in the intervention.

Topic guides will be developed in collaboration with clinical expert team and PPI contributors including adults with CP. The topic guides will be piloted with at least two adults with CP. Adaptations will be made to ensure the interviews are accessible and inclusive. This may include providing the topic guide in advance, using alternative systems of communication (using images as prompts), and pictorial memory aids. We will also offer conducting the interviews over two or more segments to minimise fatigue. The interviews will be conducted in person, by telephone or by Microsoft Teams, based on participant preference. In person interviews will be conducted in a private, accessible and comfortable setting that is free from distractions and allows for privacy and confidentiality. Interviews will be audio-recorded and transcribed verbatim.

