## Data analysis

### Quantitative data analysis

To determine the demand of the programme, descriptive statistics will be used to report the number and proportion of participants who responded to invitations, potentially eligible participants identified over a 3-month period who meet the inclusion criteria, who agree to participate in the study, excluded from the study and who drop-out during the study.

To determine the fidelity of the programme, descriptive statistics will be used to report the number of sessions attended by participants and those who completed the exercise contents.

As this is a feasibility study, analyses of outcomes will be exploratory and are not intended to provide definitive evidence of effectiveness. To determine potential efficacy, we will explore changes in outcomes over time. Continuous PROMIS outcomes will be analysed using linear mixed models to examine changes between groups over time. The Functional Mobility Scale (FMS), an ordinal measure, will be analysed descriptively and explored using appropriate non-parametric or ordinal methods where feasible. Outcomes will be interpreted descriptively in line with the feasibility design, with reference to established scoring approaches for PROMIS measures where available. Where data are missing, analysis will be conducted on available cases, and patterns of missingness will be explored descriptively. Multiple imputation methods will not be applied. STATA version 18 will be used for analysis.

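### The weekly home-exercise survey, as described, records only whether the twice-weekly target was met, so one home session reads the same as none and home dose can only be bounded

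*Protocol article*

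**What the plan says.** The section on the intervention group sets out "an online exercise class once per week" over 8 weeks and adds a home component: "Participants will also be encouraged to repeat the exercises independently twice per week between sessions".

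The two parts are measured differently:

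- **Supervised part.** Attendance is recorded, and "The number of sets and repetitions performed during supervised sessions will also be recorded".
- **Home part.** The intervention section describes "a brief self-reported survey capturing whether participants completed the prescribed exercises independently at least twice per week". The Implementation section makes the survey weekly and describes it in nearly the same way: "a brief weekly survey indicating whether they completed the prescribed exercises independently at least twice per week in addition to the supervised session".

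The Implementation section gives this self-report a specific role: "Self-reported completion of the prescribed exercise programme to evaluate fidelity of intervention content". For the analysis, the Quantitative data analysis section says that "descriptive statistics will be used to report the number of sessions attended by participants and those who completed the exercise contents". No count, diary or video-access log of home sessions is described in the article.

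**The concern.** Both descriptions of the home measure are a yes/no answer against a threshold of two sessions. A 'no' week therefore covers both zero sessions and one session, and nothing else in the article separates them.

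The objectives include describing fidelity, and the Outcomes section says the findings will inform progression to a larger trial. If many weeks come back 'no', the team will have to choose between lowering the home target, adding support and dropping the home component. Regular single sessions and no home exercise at all point to different choices.

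The distinction also bears on the article's own benchmark. The Background cites structured exercise in CP as typically performed 2–4 times a week. A participant who attends the class and does one home session reaches two a week, which is inside that range. One who attends and does none stays at one a week, below it. The survey records both as 'no'.

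**Working it through.** **Inputs.** One class a week for 8 weeks and two encouraged home sessions a week (intervention section); a yes/no survey each week with threshold 2 (Implementation section); 30 participants in the intervention arm (Participants section). The article gives no total for intended sessions, so there is no figure of its own to reproduce.

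**Share of the programme done at home.**
- Supervised: 8 × 1 = 8. Home: 8 × 2 = 16. Total: 24.
- Home share: 16/24 = 67%.
- If only the 7 gaps between the 8 classes count, home is 7 × 2 = 14 and the share is 14/22 = 64%. The point is unchanged.

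**Bounds on one participant's home dose.** Let k be the number of 'yes' weeks out of 8, with all surveys answered. Credit each 'yes' week with the prescribed 2 sessions; each 'no' week holds 0 or 1.
- Lower bound: 2k + 0 × (8 − k) = 2k.
- Upper bound: 2k + 1 × (8 − k) = k + 8.
- Width: 8 − k.

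| 'Yes' weeks (k) | Home sessions of 16 | Share of intended |
|---|---|---|
| 0 | 0–8 | 0–50% |
| 2 | 4–10 | 25–62.5% |
| 4 | 8–12 | 50–75% |
| 6 | 12–14 | 75–87.5% |
| 8 | 16 | 100% |

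A 'yes' week can also hold more than two sessions, so without the cap the upper bound would be open.

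**Arm level.** 30 × 8 = 240 person-weeks and 30 × 16 = 480 intended home sessions. If half the person-weeks are 'yes' (an assumption for illustration), the lower bound is 120 × 2 = 240 and the upper bound is 240 + 120 = 360. Home dose would be reported as somewhere between 50% and 75% of that intended.

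**Order of participants.** Take two participants with a and b 'yes' weeks, a < b. The one with fewer can have done more home sessions when a + 8 > 2b. Going through b:
- b = 1: a = 0 (1 pair)
- b = 2: a = 0, 1 (2 pairs)
- b = 3: a = 0, 1, 2 (3 pairs)
- b = 4: a = 1, 2, 3 (3 pairs)
- b = 5: a = 3, 4 (2 pairs)
- b = 6: a = 5 (1 pair)
- b = 7 or 8: none

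That is 12 of the 36 possible pairs. For example, 2 'yes' weeks plus six weeks of one session is 2 × 2 + 6 × 1 = 10 sessions. Four 'yes' weeks plus four weeks of none is 4 × 2 + 4 × 0 = 8. The first participant did more, yet reads as half as adherent (2 of 8 weeks against 4 of 8).

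**The case against.** The strongest objection is that the survey form is not shown. Both descriptions are single sentences in a journal article and may state the purpose of the item, not its response options. A count with a derived indicator would fit them. That possibility stands, and it is why the point is made about the measure as described. But the article describes the measure twice, each time as a threshold, and the analysis section likewise speaks of those who completed the exercises. If no count is collected, no analysis plan can recover it later.

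Second, the item matches the stated target. Participants are encouraged to exercise twice a week, and the survey asks whether they did. The proportion of weeks on target is a legitimate fidelity summary, and the article promises no total home dose, dose-response analysis or progression cut-off based on home sessions. This is right and limits the impact. It does not supply the size of the shortfall in the other weeks.

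Third, no planned analysis ranks participants, and the 12 of 36 pairs says only that a reversal is possible, not how likely. That also stands. The figure illustrates how coarse the item is and is not a predicted error rate.

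Fourth, a short item may suit a population with varied communication and cognitive needs, and a recalled count is still unverified self-report. This is a fair caution, but a single choice from 0 to 3 or more is a small addition.

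The planned "semi-structured interviews with 15 adults with CP who participated in the online exercise programme" may explain why home exercise was not done. They cannot supply counts for an arm of 30.

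**Conclusion.** The concern holds. As described, the survey shows how often the twice-weekly target was met but not how far short the remaining weeks fell. About two thirds of the intended sessions are affected. A participant's home dose is known only to within 8 − k sessions, from a range of 0–8 of 16 when no week is on target to an exact value when all are.

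This rests on three assumptions: the survey asks what the two sections say it asks, all eight weekly surveys are answered, and sessions beyond two a week are not credited. Missing surveys would widen the ranges.

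The consequence is limited to the fidelity description and the progression decisions drawn from it. Randomisation, the PROMIS analyses and the measurement of supervised sessions are unaffected. The change is worth making because it is cheap and the information cannot be recovered afterwards. Confidence is medium, because the form itself could not be seen.

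**What to change.** In the existing weekly survey, ask how many times the exercises were done independently that week, with options 0, 1, 2, and 3 or more. Derive the planned at-least-twice indicator from the answer, so nothing already planned is lost. In the Quantitative data analysis section, add the distribution of weekly home sessions to the descriptive fidelity summary. For answered weeks, the dose credited up to two a week is then known without a range, subject to the limits of self-report.

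If the form already asks for a count, only the wording in the intervention and Implementation sections and the analysis summary needs to change. If delivery has begun, use the count for the remaining weeks.

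The cost is one response format, one line of descriptive reporting, a slightly longer recall item and possibly a minor ethics notification. No extra visit, form or analysis method is needed.
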